### Study intervention

#### Baclofen intervention

Clinical trials on baclofen for alcohol dependence treatment have used baclofen at a dose of 30 mg ⁄d [29-31] over 30 to 120 days. This is within the low therapeutic range for muscle spasms. However, Garbutt and colleague’s [32] suggested that 30 mg of baclofen per day may be an insufficient dose for some patients to achieve abstinence. Additionally, baclofen effectiveness for GHB dependence could be smaller, since tolerance may occur due to recent abuse of GHB and a possible substitution function (as treatment will be started immediately after detoxification).

Based on these results and the unpublished results of a small dose finding experimental treatment study in our treatment center, where patients reported limited effect of baclofen 30 mg per day, we decided to administrate a dose of 45 mg to a maximal dose of 60 mg per day orally to avoid the risk of (co) intoxication. In this study baclofen will be administrated orally three times daily as usually recommended [22] and started with a total dose of 15 mg per day. During the first 10 days baclofen will be gradually increased with 15 mg per day every 3 days up to the chosen minimum dose of 45 mg, or a maximum dose of 60 mg in case no effect is reported at 45 mg after 2 weeks. This dose will subsequently be maintained for a period of 10 weeks. Successively, baclofen will be tapered off to 0 mg in 2 weeks (see Table 1). Patients will be asked to avoid abrupt termination of baclofen and will be guided by their physician to avoid complications of baclofen withdrawal. Patients who wished to continue the baclofen treatment will be offered an outpatient counselling and medication by their physician for another 3 months.

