**Table 1 Tab1:** **Baclofen dose in mg/week**

**Week**	**1**	**2**	**3**	**4**	**5**	**6**	**7**	**8**	**9**	**10**	**11**	**12**	**13**	**14**	**15**
Doses a day	15–30	45–60	45/60	45/60	45/60	45/60	45/60	45/60	45/60	45/60	45/60	45/60	30–45	15–30	15–0

Compliance will be assessed based on self-report, urine test for GHB, and empty pill counts. The physician will make use of the BRENDA method, a psychosocial program designed to enhance medication and treatment compliance [33,34]. In case of GHB use during baclofen treatment, participants are expected to contact the research physician. In case of relapse, immediate cessation of treatment will be considered to avoid intoxication hazards.

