#### Additional measures

Addiction physicians will be asked to monitor withdrawal symptoms when tapering baclofen, using standard questions. These include a short check of the most reported withdrawal symptoms in the literature [43,44].

We will monitor the use of other substances over the last thirty days (number of days and quantity) using section 1 of the Measurement of Addicts for Triage and Evaluation (MATE) before and after detoxification and at follow up (3 months). The MATE is a Dutch instrument designed as an aid in the diagnosis of clinically relevant patient characteristics in substance use disorders according to the DSM-IV axes [45].

At 6 month period we will also report on the needed period of treatment with baclofen to maintain abstinence by monitoring relapse (Timeline Follow back) and craving assessment (DDQ, VAS) within the intervention group between those who used baclofen for 3 month only and those who choose to continue the treatment further.

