### Procedure and data collection

Patients in all treatment conditions (baclofen + TAU or TAU only) will be assessed by research assistants identically in the following time points. Before detoxification, the intensity of GHB abuse (MATE), Quality of life (EQ-5D) and psychiatric comorbidity (DASS) will be assessed. At the end of the detoxification treatment (baseline) and at follow up (three months after start of detoxification) craving (VAS, DDQ), psychiatric comorbidity (MINI plus, DASS), and Quality of life (EQ-5D) will be assessed.

The addiction physician will monitor the participants in the baclofen condition during regular medical check-ups for potential side effects (side effect checklist) and craving (VAS, DDQ), see Table 2. During the follow-up (six months after start of detoxification) the DDQ, DASS, MINI-plus, EQ-5D will be repeated. In summery self-report questionnaires will be administered at the start of detoxification; start of baclofen treatment (week 0), baclofen titration and stabilization (week 1 + 2) and maintenance treatment (week 3–12). Add to that, three months after the end of the baclofen treatment, a follow-up measurements will take place. The research assistant will build up an online Client Record Form from all the questionnaires filled in by the patients. A summary of the medical records will be added by the physician to the electronic patient file.

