### Statistical analyses

Descriptive analysis will be executed for all measurements and will include the mean, SD and frequencies of events with confidence intervals. Descriptive statistics will be used to compare the basic characteristics of the participants in the experimental group and the control groups. To assess any difference in relapse rates between the experimental group and the control groups (TAU group and matched historical group) at 3 month after detoxification Pearson Chi-squared test will be used for the dichotomous abstinence rates. ANOVA will be carried out on continuous variables, such as the total number of abstinent days, the maximum duration of continued abstinence, time before relapse (relapse defined as ≥ 3 times GHB use per day, for 2 subsequent days), and level of substance use over a period of 3 months. At 6 months period participants who continued baclofen will be compared to those who have stopped with baclofen (after 3 month) on relapse into GHB abuse or abstinence corrected for craving. The numbers of patients maintaining abstinence will be analysed with the intention-to-treat principles. The difference in craving will be analysed by MANCOVA at 3 months between groups (abstinent experimental versus abstinent TAU or relapsed TAU) with DDQ and VAS craving as dependent variables and corrected for craving levels immediately after detoxification. The change in craving in time during the baclofen treatment will be analysed via repeated measures MANOVA. By means of MANCOVA at 6 months after detoxification the difference in craving among participants who are still using baclofen and those who have discontinued baclofen will be analysed corrected for craving after 3 months. The effect of baclofen on the psychiatric symptoms levels (DASS, MINI) and also quality of life (EQ–5D) will be analyzed similarly as for craving at 3 and 6 months. The effects of the different TAU approaches as potential confounders will be tested in a sensitivity analyses (changing one-factor-at-a-time) in an linear regression including TAU per center as covariates.

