## Discussion

This study protocol presents the design of an open label clinical trial evaluating the efficacy of baclofen to prevent relapse, reduce craving and anxiety, and to assess the safety profile of baclofen in GHB dependent patients. To date, there are no reports on the potential of baclofen to prevent relapse in GHB dependent patients. We expect that baclofen will increase abstinence rates, reduce craving and will be well tolerated. In addition, baclofen may improve psychiatric symptoms such as anxiety and depression, as suggested in several clinical trials in alcohol-dependent individuals [29,30,46].

Several risks of baclofen use are taken into account in the current study. In patients with neuropsychiatric disorders, such as schizophrenia, severe depression, mania, Parkinson’s disease and cerebrovascular diseases, exacerbations of these conditions may occur, when the dose of baclofen is rapidly increased. It may lower the threshold for seizures in epileptic patients [42]. To limit these risks in the current trial, baclofen will be uploaded gradually, over a period of minimally 10 days. Moreover, patients previously diagnosed with any of the mentioned diseases will be excluded from the study.

Abrupt discontinuation of baclofen, when used for several months, can be associated with a withdrawal syndrome which resembles benzodiazepine and alcohol withdrawal. Several symptoms are reported such as hallucinations, fever, confusion, delirium, agitation, insomnia, and muscle stiffness and spasms [47]. Therefore, patients will be advised to taper down slowly when discontinuation is needed.

Intoxication with baclofen has been reported in doses above 100 mg [48]. This risk increases if patients combine baclofen with GHB. Intoxication is not expected when baclofen is administered at a low dose (<30 mg per gift), as applied in the current study. Patients will however, be informed repeatedly of this potential risk and the treatment will be discontinued immediately in case of relapse.

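### The six-month craving, symptom and quality-of-life comparisons are worded by current baclofen use, which later relapse can change, while Additional measures defines the craving comparison by the patient's choice at month 3

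*Protocol article*

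**What the plan says.** Protocol article, Statistical analyses: the six-month craving analysis is a MANCOVA within the baclofen arm, in which "the difference in craving among participants who are still using baclofen and those who have discontinued baclofen will be analysed corrected for craving" at month 3. The groups are described by status, with no date by which a patient must have stopped and no reference to the reason. Psychiatric symptoms (DASS, MINI) and quality of life (EQ-5D) "will be analyzed similarly as for craving at 3 and 6 months", so they inherit the same groups.

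Protocol article, Additional measures: the six-month comparison of relapse and craving (DDQ, VAS) is "between those who used baclofen for 3 month only and those who choose to continue the treatment further". This split is by the decision at month 3. Its stated purpose is to report how long baclofen is needed to maintain abstinence.

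Protocol article, Baclofen intervention: the extension is optional. "Patients who wished to continue the baclofen treatment will be offered an outpatient counselling and medication by their physician for another 3 months". The text below Table 1 adds: "In case of relapse, immediate cessation of treatment will be considered to avoid intoxication hazards". The Discussion is firmer: "the treatment will be discontinued immediately in case of relapse". Neither statement is limited to the first 12 weeks.

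**The concern.** The two sections define one contrast in two ways, and they disagree on patients whose outcome is poor. Take a patient who chooses to continue at month 3, relapses at week 18 and is taken off baclofen. Under Additional measures this patient is a continuer. Under the craving sentence in Statistical analyses the patient has discontinued.

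Under the second rule an event after month 3, relapse, helps to decide the group. If relapse goes with higher craving, more symptoms and lower quality of life, the group still on baclofen is cleared of some poor outcomes and the other group receives them. The comparison then favours continued treatment even when continuing has no effect. The covariate, craving at month 3, is measured before the relapse and cannot correct for it. The result would feed directly into the statement on the treatment period needed.

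**Working it through.** **1. Where the week-18 relapser is counted**

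| Source | Basis of the groups | Group if taken off baclofen |
|---|---|---|
| Additional measures (relapse, DDQ, VAS) | choice at month 3 | continued |
| Statistical analyses, craving MANCOVA | use at six months | discontinued |
| Statistical analyses, DASS, MINI, EQ-5D | as for craving | discontinued |

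**2. Inputs from the protocol (Sample size calculation)**

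The plan's own figures reproduce: (1.96 + 0.84)² × (0.7 × 0.3 + 0.36 × 0.64) / 0.34² = 7.84 × 0.4404 / 0.1156 = 29.87, so 30 per group; 30 / 0.75 = 40 in the baclofen group. None of these figures is in dispute.

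At the expected 70% abstinence, 40 × 0.70 = 28 patients reach week 12 abstinent. With 25% drop-out, 30 × 0.70 = 21.

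**3. Inputs assumed (not in the protocol)**

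Half of the patients continue. Relapse in months 3 to 6 is r = 0.30 in both groups. A share s of relapsed continuers is taken off baclofen. Craving is 1 SD higher after relapse. The choice to continue is unrelated to prognosis, and continuing has no effect.

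**4. Relapse proportions by current use**

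- Still using: r(1 − s) / (1 − rs).
- Discontinued: r(1 + s) / (1 + rs).
- s = 1: 0 versus 0.60 / 1.30 = 46%. At n = 28, 14 × 0.3 = 4.2 patients move.
- s = 0.5: 0.15 / 0.85 = 18% versus 0.45 / 1.15 = 39%. At n = 28, 2.1 patients move.

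With a 1 SD shift, the spurious difference is the gap between the proportions: about 0.46 SD (s = 1) or 0.391 − 0.176 = 0.215 SD (s = 0.5).

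**5. Simulation under no effect of continuing**

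There were 6,000 runs per setting. Six-month craving had correlation 0.5 with month-3 craving, and DDQ and VAS had correlation 0.6 (both assumed). The analysis was a two-score MANCOVA adjusted for both month-3 scores. Groups are by current use.

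| n | r | Shift | s | Spurious difference | False positives |
|---|---|---|---|---|---|
| 28 | 0.3 | 1 SD | 1 | 0.46 SD | 15.5% |
| 28 | 0.3 | 1 SD | 0.5 | 0.22 SD | 7.4% |
| 21 | 0.3 | 1 SD | 1 | 0.45 SD | 10.7% |
| 21 | 0.3 | 1 SD | 0.5 | 0.20 SD | 6.1% |
| 28 | 0.3 | 0.5 SD | 1 | 0.23 SD | 7.9% |
| 28 | 0.3 | 0.5 SD | 0.5 | 0.10 SD | 5.9% |
| 28 | 0.2 | 0.5 SD | 0.5 | 0.08 SD | 5.4% |
| 28 | 0.5 | 1 SD | 1 | 0.67 SD | 24.7% |

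A repeat of the n = 28, 1 SD, r = 0.3 settings gave about 0.45 SD and 15% (s = 1) and 0.20 SD and 7% (s = 0.5). Grouping by the month-3 choice gave about 0 SD and 4.3 to 5.7%.

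**6. If the choice is related to prognosis**

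Let an unmeasured risk act on both choice and relapse (log-odds 1 per SD each, n = 28). Grouping by choice then gives 0.15 SD and about 6%. Grouping by current use gives 0.50 SD and 19.5% (s = 1) or 0.31 SD and 9.8% (s = 0.5). The choice-based split reduces the bias but does not abolish it.

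**7. What the illustration leaves out**

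Read literally, the discontinued group also takes in patients stopped for relapse before week 12. At 70% abstinence up to 40 − 28 = 12 of 40 patients relapse by then. Month-3 craving would adjust for that part only partly.

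**The case against.** The best defence is that the craving sentence is shorthand. Additional measures names the same arm, time point and craving scales and gives a choice-based split, so the analysis sentence may only be attaching a test to those groups. A condensed article may also leave the handling of later stoppers to the full protocol. This reading is possible, but nothing in the article says so, and the sentence does state a rule of its own. If it is shorthand, the fix only makes that explicit.

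The link from relapse to stopping is also less firm than the Discussion suggests. The Methods text says only that stopping is considered, and neither passage mentions the extension. That stands as a reason for caution about size: with half of relapses leading to a stop, false positives are only 6 to 7%. It does not remove the direction, because neither passage excludes the extension.

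An on-drug contrast can be a fair exploratory question, given the authors' interest in a substitution effect. That too stands, which is why actual use should still be described.

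Two stronger readings are tempting but not supported. First, a reader might infer that the six-month relapse sentence also contradicts the craving sentence. It says that "participants who continued baclofen will be compared to those who have stopped with baclofen (after 3 month) on relapse into GHB abuse", and the words in brackets can mean stopping at month 3 or at any time after it. On the second meaning the two sentences agree, so this is ambiguity rather than clear conflict. Second, a reader might infer a timing error from Procedure and data collection, where "three months after the end of the baclofen treatment, a follow-up measurements will take place". Counted from week 12 that is week 24; counted from the end of the taper at week 15 it is later; for patients in the extension it is later still. Table 2 nevertheless fixes the baclofen group's follow-up at week 24, so no change is needed there.

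**Conclusion.** The concern holds in a limited form. The analysis section words the six-month craving comparison, and with it DASS, MINI and EQ-5D, by current baclofen use. Additional measures defines the craving comparison by the month-3 choice. Taken literally, the first rule moves relapsed continuers into the comparator and favours continued baclofen.

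Only the direction rests on the protocol, together with the modest assumption that relapse worsens these outcomes. The size rests on the assumed shares, relapse rate, craving shift and correlations. At n = 28, with half continuing, 30% relapse and a 1 SD shift, it is about 0.2 SD with 7% false positives if half of relapses stop baclofen, and about 0.45 SD with 15% if all do. The other settings run from 0.08 SD (5%) to 0.67 SD (25%).

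This is a minor matter: a secondary, self-selected contrast within one arm of a study that describes itself as explorative. A reader might infer that the main efficacy result is biased by the same route. It is not: the primary three-month comparison is between baclofen and the control groups and does not use this split, and the sample size is unaffected.

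**What to change.** In Statistical analyses, define the groups for every six-month comparison (relapse, craving, DASS, MINI, EQ-5D) as in Additional measures:

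- Group patients by the recorded week-12 choice to continue or stop, among those still on baclofen at that visit.
- Keep each patient in that group whatever happens later, including stopping because of relapse.
- Describe patients who stopped before week 12 separately.
- Report actual baclofen use at week 24 descriptively only.
- State that continuing is self-selected, so the result remains exploratory.

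The cost is a short passage of text and recording the week-12 choice; no visits or patients are added. The price in interpretation is a diluted on-drug contrast, because continuers who relapse and stop stay in their group. Self-selection remains.

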### Aims and hypotheses

The primary aim of the current study is to assess the potential of baclofen to prevent relapse in recently detoxified GHB-dependent patients. We hypothesize that administration of baclofen to GHB-dependent patients after detoxification is associated with decreased relapse rates as compared to treatment as usual (without baclofen). We also hypothesize that treatment with baclofen is associated with reduced levels of craving for GHB and reduced psychiatric symptoms levels, including anxiety, and increased quality of life. We expect baclofen treatment to cause minimal side effects in these patients. Finally, we expect a lower drop-out rate from adjuvant therapy (TAU) in the intervention group.

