#### In- and exclusion criteria

Patients are eligible to participate if GHB dependence (according to the DSM-IV general criteria of dependence) is their primary diagnosis [28] and their age is at least 18 years. All participants should be able to read and speak the Dutch language. Patients with any current somatic or psychiatric safety concerns are excluded. Exclusion criteria are liver cirrhosis and impaired renal function (as indicated by aspartate aminotransferase (AST)), alanine transaminase (ALT), or gamma-glutamyl transferase ((GGT) level >3 times the upper limit of normal (ULN); bilirubin > ULN; serum creatinine > ULN), unstable hypertension, unstable diabetes mellitus, seizure disorder including patients currently taking anticonvulsants, and pregnancy. Patients experiencing current severe mood disorder (bipolar disorder or major depressive disorder), current psychotic disorder (including schizophrenia), and/or suicidal ideations and patients suffering Parkinson’s disease will be excluded too. Co-current use of anxiolytics, stimulants or hypnotics will not be permitted.

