#### Secondary outcome measures

The secondary outcomes as listed below are;

The craving level, as indexed by self-report using the Desire for Drugs Questionnaire (DDQ) and a visual analogue scale (VAS). The DDQ is validated instrument [35] which measures an instant desire, triggered by internal or external cures (instant craving). Franken and colleagues [35] identified three factors as underlying dimensions, namely ‘desire and intention’ (seven items), ‘negative reinforcement’ (four items), and ‘control’ (two items) with a scale from 1 (totally disagree) to 7 (totally agree). The total score exists of 14 items with a sum score between 14 and 98 [35]. In addition to that patients were asked to rate craving for GHB by means of a visual analogue scale (VAS) on a Vertical line from no craving at all (at the bottom) with a score of 0, to extremely strong craving (at the Top) with a score of 100. The result is a score on a continuous scale ranging from 0 to 100.

A change in psychiatric symptoms will be measured by means of the Mini International Neuropsychiatric Interview-plus (MINI-plus) and Depression Anxiety Stress scale (DASS). A trained therapist or physician will apply the MINI-plus. It is a structured interview to assess the main Axis I psychiatric disorders based upon the DSM–IV and ICD-10 criteria. It is used to determine current and lifetime psychiatric disorders [36]. The MINI is shown to have good psychometric properties and is reliable for the detection and classification of psychiatric comorbidity [37]. The DASS self-report will be used to measure psychiatric symptom levels and the related negative emotional states along the 3 axes of depression, anxiety and stress. It is a 21-item self-report instrument. Participants are asked to use a 4-point severity scales to rate the extent to which they have experienced each state over the past week. Scores for Depression, Anxiety and Stress are calculated by summing the scores for the relevant items. For each scale threshold values are proposed and are interpreted in 5 severity intensities: normal, mild, moderate, severe and extremely severe. Thresholds as (for Depression ≥ 21; for Anxiety ≥15; for Stress ≥ 26) indicate a severe or extremely severe distress state [38,39].

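### The MINI-plus, a diagnostic interview with no defined score, is analysed as a symptom level in the manner of the craving scores; it needs a categorical analysis

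*Protocol article*

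**What the plan says.** Protocol article, Secondary outcome measures, gives two instruments one role: "A change in psychiatric symptoms will be measured by means of the Mini International Neuropsychiatric Interview-plus (MINI-plus) and Depression Anxiety Stress scale (DASS"). It then describes them differently. Of the MINI-plus it says: "It is a structured interview to assess the main Axis I psychiatric disorders based upon the DSM–IV and ICD-10 criteria". It adds: "It is used to determine current and lifetime psychiatric disorders", and that the MINI "is reliable for the detection and classification of psychiatric comorbidity". No score is given. Of the other instrument it says: "The DASS self-report will be used to measure psychiatric symptom levels and the related negative emotional states along the 3 axes of depression, anxiety and" (the third axis is stress), using 21 items rated over the past week and summed into three scales.

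Statistical analyses puts both under one label, "The effect of baclofen on the psychiatric symptoms levels (DASS, MINI"), and, together with the EQ-5D, gives them an analysis similar to that of craving at 3 and 6 months. The craving analysis at both times is MANCOVA. The 3-month model has the DDQ and VAS as dependent variables and is corrected for craving just after detoxification. The 6-month model compares continued with stopped baclofen and is corrected for craving at 3 months. The same section uses a Pearson chi-squared test for dichotomous abstinence.

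In- and exclusion criteria removes "Patients experiencing current severe mood disorder (bipolar disorder or major depressive disorder), current psychotic disorder (including schizophrenia), and/or suicidal ideations". Table 2 schedules the MINI-plus at weeks 0 and 12 in both groups and at week 24 in the baclofen group only.

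**The concern.** The stated method does not match the data that the plan says the instrument produces. MANCOVA needs continuous dependent variables with a common covariance structure, and correction for the earlier level needs a baseline that varies. A diagnosis is present or absent, its variance is tied to its prevalence, and where nobody has the disorder at week 0 the covariate is a constant.

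There is also a question of what the measure can register. The hypothesis is one of "reduced levels of craving for GHB and reduced psychiatric symptoms levels, including anxiety, and increased quality of life". That is a statement about degree. A patient can improve a good deal without crossing a diagnostic threshold. If the MINI-plus is reported as a symptom-level result, a null finding could be read as evidence against a symptom effect when it partly reflects a coarse measure and a restricted population.

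**Working it through.** **1. Group sizes.** The plan gives no figure for the MINI-plus. Its sample size for abstinence reproduces: (1.96 + 0.84)² × [0.7 × 0.3 + 0.36 × 0.64] / 0.34² = 7.84 × 0.4404 / 0.1156 = 29.87, so 30 per group; 30 / (1 − 0.25) = 40 in the baclofen group. These serve below only as group sizes.

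**2. Instrument against analysis.**

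| | MINI-plus | DASS | Craving (DDQ, VAS) |
|---|---|---|---|
| Described as | diagnostic interview | symptom-level self-report | self-report score |
| Yields | current and lifetime disorders | three summed scales | summed score; 0–100 scale |
| Analysis | as for craving | as for craving | MANCOVA, earlier level as covariate |

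The DASS fits the last row. The MINI-plus does not, unless some score is defined, and none is.

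**3. Which diagnoses can move in screened patients.**
- Lifetime diagnoses can persist or appear; they cannot remit.
- Current severe mood disorder, psychotic disorder and suicidal ideation are excluded. Where the criteria are applied, few or no patients have them at week 0, so there is little or nothing to improve. New onset remains possible.
- Other current disorders, such as anxiety disorders, are not excluded and can remit or appear. The documents give no prevalence. If 20–30% is assumed, 0.20 × 40 = 8 to 0.30 × 40 = 12 baclofen patients have one at week 0, or 6 to 9 of the 30 left after 25% dropout.

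**4. Loss of sensitivity (illustration; these assumptions are not in the documents).** Suppose a normally distributed symptom score, shifted between groups by d = 0.5 or 0.8 SD, with a diagnosis made above a threshold that 20%, 30% or 50% of controls exceed at 3 months.

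- Continuous score: power = Φ(d√(n/2) − 1.96). With d = 0.5 and n = 30: Φ(0.5 × √15 − 1.96) = Φ(−0.02) = 49%.
- Diagnosis: with control prevalence p₁, the baclofen prevalence is p₂ = 1 − Φ(z + d), where z = Φ⁻¹(1 − p₁). For d = 0.5, p₁ = 0.20, 0.30, 0.50 gives p₂ = 0.090, 0.153, 0.309.
- Power for two proportions = Φ{[(p₁ − p₂) − 1.96√(2p̄(1 − p̄)/n)] / √([p₁(1 − p₁) + p₂(1 − p₂)]/n)}, where p̄ is the mean of p₁ and p₂. For p₁ = 0.20 and n = 30: (0.110 − 1.96 × 0.0909) / 0.0898 = −0.76, so 22%.

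| n per group | d | Continuous score | Diagnosis, p₁ = 20% / 30% / 50% |
|---|---|---|---|
| 30 | 0.5 | 49% | 22% / 27% / 32% |
| 30 | 0.8 | 87% | 42% / 53% / 65% |
| 40 | 0.5 | 61% | 29% / 35% / 41% |
| 40 | 0.8 | 95% | 53% / 65% / 78% |

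These are unadjusted normal approximations. They are rough where few cases are expected, for example 0.090 × 30 = 2.7 in the baclofen group. The table shows a clear loss of power, but power well above zero.

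**The case against.** The strongest objection is that little depends on this. The DASS is a past-week severity measure taken in both groups at weeks 0 and 12, and it already tests the symptom hypothesis. That stands, and it limits the severity.

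Next, the article never names MANCOVA for the MINI-plus. It promises event frequencies with intervals for all measurements, uses chi-squared where an outcome is dichotomous, and as a condensed article may leave scoring to a fuller document. This stands in part: MANCOVA is inferred. But it is the natural reading, since the plan refers the MINI-plus to the craving analysis and names no other method. The text has fixed a method, not left one open.

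A reader might go further and infer that the MINI-plus cannot show the hypothesised improvement, so that a null result is built in. The documents do not support this:
- The interview covers current disorders and is repeated at week 12 in both groups. Anxiety, which the hypothesis names, is not an excluded diagnosis.
- The 3-month comparison is between groups. Even from a baseline of zero, fewer new disorders on baclofen would be a difference, and the Background cites rising anxiety and depression after stopping GHB as a reason for relapse.
- Nothing makes lifetime diagnoses an outcome; the phrase describes the instrument.
- The floor is only partly established. The mood-disorder exclusion is qualified as severe, and Study design bases assignment partly on the eligibility criteria, so TAU may include patients who did not meet them.
- The plan does not say that DASS and MINI-plus enter one multivariate test, so a dilution of the DASS result is conjecture.

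**Conclusion.** The plan labels a diagnostic interview a symptom level and refers it to an analysis built for continuous scores. That mismatch follows from its own description of the instrument and should be corrected. The MINI-plus is coarse and less sensitive for this purpose; it is not incapable of showing change.

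The size depends on assumptions. In the illustration, replacing a score by a diagnosis takes power at 30 per group from 49% to 22–32% for a 0.5 SD shift, and from 87% to 42–65% for 0.8 SD. The conclusion about method does not depend on these figures. It rests on two readings: that an analysis similar to that of craving means MANCOVA, and that the MINI-plus yields categories because no score is defined.

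Severity is minor to moderate. The outcome is secondary, the Discussion calls the study explorative, and the primary result is unaffected.

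**What to change.** Amend Secondary outcome measures and Statistical analyses as follows.

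1. Let the DASS depression, anxiety and stress scales carry the symptom-level hypothesis, and take the MINI-plus out of the MANCOVA.
2. At 3 months, analyse current MINI-plus disorders as a binary outcome (present/absent), comparing baclofen plus TAU with TAU only, by logistic or exact regression adjusted for week-0 status.
3. Report new onset of the excluded disorders as a count by group.
4. Use lifetime diagnoses only as a baseline characteristic.
5. At 6 months Table 2 provides no MINI-plus in the TAU group. Restrict that analysis to continued versus stopped baclofen within the baclofen group, adjusted for month-3 status, or report it descriptively if events are sparse.

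The cost is wording in two sections and no new data. The price is that the MINI-plus becomes a supportive categorical result and, with groups of 30 to 40, an imprecise one.
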